#### c) Outcomes for the estimation of cost-effectiveness

The collection of cost and outcome data within phase 3 will mirror the approaches in phase 1, i.e. generic measurement of preference-based health-related quality of life using the EQ-5D and cost components that will allow for the estimation of back pain-specific and generic costs associated with the 6 month period following participants' initial consultation. In addition to the estimate of cost-effectiveness for the subgrouping approach (see 'Data analysis' section) we will explore whether there is evidence for sustainability. We anticipate that improved primary care for patients with LBP will reduce demands on secondary care for further investigation and management.

### Sample Size

#### Health care practitioners

We aim to involve a minimum of 20 GPs and 20 physiotherapists in the questionnaire surveys of phases 1 and 3, from the participating GP practices and related physiotherapy services.

#### Patients

Scoping work in preparation for this study has provided us with information on rates of consultation and current referral pathways, by which we can assess the expected recruitment and determine the power we will have to detect clinically important changes in patient outcome. The consultation rate for back pain in local general practices ranges from 6-10% annually. We aim to invite 7 GP practices (population of approx 45,000 adults aged 18 years or over) from which we expect at least 2,700 LBP consulters per year. Previous research suggests that approximately 50% of patients will be willing to consent to completing the questionnaires [45]. Based on these figures, we anticipate that within the timeline of the study (across both phases 1 and 3), recruitment of 1000 patients should be feasible.

A difference of 2.5 points in RMDQ [37] change scores is considered to be a minimum clinically important difference [46]. We wish to test the superiority of the subgrouping for targeted treatment system (phase 3) over usual primary care (phase 1) in relation to this 2.5 point difference for those patients in the high and medium risk subgroups, and to test for non-inferiority of the new care system compared to usual care in the low risk subgroup. A weighted sample size (based on the timeline ratio of 1:2 (phase 1: phase 3) of 50 patients (phase 1) and 100 patients (phase 3) is powered at about 80% to detect a 2.5 point difference, assuming a standard deviation of 5 and using a 5% two-tailed significance level. Based on our pilot work, we expect 20% of back pain patients to be classified as at "high-risk" of poor outcome, 40% to be at "medium-risk" and 40% at "low-risk". Thus, our expected study size of 1000 patients will enable us to evaluate this clinical difference across the three risk subgroups, and has 80% power to detect a 'small' effect size of about 0.2, equivalent to a mean difference in RMDQ scores of approximately 1, over the total study population (taking into account 20% loss to follow up).

### Data analysis

#### Health care practitioners' attitudes and behaviour and care processes

A descriptive summary of the characteristics of the participating GPs and physiotherapists will be provided. To assess differences in health care practitioners' attitudes between phase 1 and phase 3, we will compare baseline mean scores and follow-up mean scores for the self-confidence and PABs scales using matched-analyses techniques (e.g. paired t-test) based on before (phase 1) and after (phase 3) matching of scores to individual health care practitioners. The matched-analyses are based on evaluating the same health care practitioners before and after; a sensitivity analysis using unmatched approaches (e.g. unpaired t-test) will be used if the pool of practitioners in phase 3 is not exactly the same as that in phase 1. As well as providing the best estimate of the true mean difference, we will also present 95% confidence interval estimates for the difference and give p-values for the statistical tests performed. Mean changes in attitudes scores (3 questionnaires: before the quality improvement interventions, immediately after the quality improvement interventions and 12 months after the quality improvement interventions) will also be described.

Behaviour measures, relating to the two case vignettes, follow categorical or textual response formats and differences over time will be described. Health care practitioner behaviour differences between time points will also be statistically evaluated by comparing data of their actual clinical practice, e.g. health care consultations, medication prescriptions, sickness certification and patterns of referral obtained from medical record downloads for patients who consent to record reviews and from physiotherapists' case report forms. Furthermore, GP responses to the computer "pop-up" prompt on 'chronicity risk' (low; medium; high) and presence of 'yellow flags' (no; yes) will be compared to patient questionnaire responses to the subgrouping tool; the percentage agreements would be expected to be higher after the quality improvement intervention. These analyses, based on patient measures, are unmatched and will follow between-group techniques i.e. unpaired t-test, chi square test and regression methods (as described below for clinical outcomes).

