#### a) Health care practitioners' attitudes and behaviour and care processes

Attitudes and reported behaviour: We will conduct a questionnaire survey of participating GPs and physiotherapists to describe their attitudes and beliefs about back pain and its management, and their reported clinical behaviour relating to two clinical case vignettes developed from real patients with LBP. The questionnaire and case vignettes have been adapted from a previous national survey of GPs and physiotherapists [7]. The self-report questionnaire will include key demographic and clinical experience questions, a measure of beliefs and attitudes towards LBP, the Pain Attitudes and Beliefs Scale (PABS) [33,34], and a measure of self-confidence in managing LBP patients [35]. Full details of the contents of the questionnaire are provided in Table 1.

**Table 1 T1:** Contents of Health Care Practitioner Questionnaire

Domain	Outcome Measures	Study Phase
**Clinical experience**	Length of time qualified	1
	Post-graduate training	1,2,3
**Self-confidence**	Self-confidence in managing back pain patients [35]	1,2,3
**Beliefs and attitudes**	Pain Attitudes and Beliefs Scale (PABS) [33,34]	1,2,3
**Reported clinical behaviour**	Clinical case vignettes of patients with non-specific low back pain with items relating to investigations, referrals, advice and medication	1,2,3
	Changes in management of low back pain following best practice updates/training programme	2,3
**Education**	Future learning needs	2,3

Care processes and actual clinical behaviour: We will collect data on health care practitioners' actual clinical behaviour from anonymised GP medical record reviews and physiotherapy case report forms, for patients who consent to the study team accessing their medical records. We aim to collect data on primary care consultations, ordering of diagnostic tests (radiographs, MRI and CT scans), prescribed medications, referrals to other professionals or services and issuing of sickness certificates. Additional data from physiotherapy case report forms will include the physiotherapist's view of the patient's key problems and targets for treatment, the treatment approaches used, the advice given and the number and length of treatment sessions.

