#### b) Patients' clinical outcomes

A consecutive sample of patients consulting with LBP at each participating practice will be recruited in phase 1 for a period of up to 6 months. As each patient consults with LBP at one of the participating GP practices and is assessed, if their GP enters a previously validated back pain Read Code [2] to indicate the reason for consultation as non-specific LBP, a "pop-up" computer prompt will remind them that the patient is eligible to be invited to participate in the IMPaCT Back study. The GP will inform the patient about the study and ask them if they are willing to receive further information by post. On the same computer pop-up screen the GP will record whether the patient is willing to receive further information about the study, in addition to recording their own clinical impression of the patient's risk of poor outcome (low, medium or high risk of poor outcome). The GP will be able to "opt out" of the computer screen pop-up if they consider the patient not eligible for the study. In phase 1, all patients will receive usual primary care, with referral to other services (including physiotherapy) as usual. There will be no subgrouping for targeted treatment in phase 1, or any specific training or additional resources for assessing and managing LBP patients.

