### The sub-grouping tools and targeted treatment approaches

Two versions of a previously developed and validated subgrouping tool for use in primary care [19] will be used. The tools include key physical and psychological predictors of outcome in LBP. A 6-item computer-based subgrouping tool will be embedded in the EMIS GP computer system, for use in real-time GP/patient consultations. Following completion, patients are categorised as either at low (a score of 2 or less) or high (a score of 3 or more) risk of poor outcome and a recommendation is made about whether or not a referral to physiotherapy is likely to be most appropriate. Patients classified as at low risk of poor outcome are recommended to receive best primary care advice and management by the GP, to include a screen for red flags, reassurance about their good prognosis, the benign nature of their pain, and simple messages and advice about pain relief, appropriate physical activity levels, return to normal activity (including work), avoiding bed rest, appropriate use of pain relieving modalities and the role of further investigations. To reinforce these key messages, a brief information sheet will be given. No onward referral to other services is recommended although patients will be advised to re-consult if symptoms persist. Patients at high risk of poor outcome are recommended to be referred to physiotherapy. The GP and patient are then able to use this recommendation in their decision-making.

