#### Clinical outcomes for patients

The primary outcome measures of patient benefit will be back pain-related disability (measured on the RMDQ [37] and pain catastrophising (measured on the catastrophising subscale of the Coping Strategies questionnaire [38] at 6 month follow up. Primary analysis of the patient data will follow the principles of "intention to treat", to compare outcomes of patients in phase 1 (pre-intervention) to those of patients in phase 3 (post-intervention). A "per-protocol" analysis, based on the evaluation of phase 3 patients who were treated with strict adherence to the subgrouping tool allocation rule (versus all phase 1 patients) will be carried out as a secondary comparison. Estimates of treatment effects, i.e. comparative outcomes for phase 1 (pre-intervention) versus phase 3 (post-intervention), with 95% confidence intervals will be calculated using linear regression (for numerical outcomes) and logistic regression (for categorical outcomes). Analyses will be carried out both unadjusted and adjusted for baseline imbalances in certain variables i.e. age, gender and baseline values of key outcomes. Statistical adjustment is necessary as this is an observational, before and after study design, and thus open to the possibility of confounding bias; adjustment will ensure parity of key baseline patient characteristics across phases 1 and 3. Analyses will be carried out at each patient follow up time point (2 and 6 months) for primary and secondary outcome measures; the primary endpoint is 6 months. Analyses will be performed on available data, and on imputed datasets based on the method of multiple imputation [47]. We will use STATA and SPSS for the analyses.

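### Physiotherapy case-report-form data are compared between phases as practitioner behaviour, but the new system is designed to change who is referred, so a changed caseload can be mixed with changed practice

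*Protocol article*

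**What the plan says.** Under Phase 1, part a), the protocol article lists what physiotherapists will record: "Additional data from physiotherapy case report forms will include the physiotherapist's view of the patient's key problems and targets for treatment", and also "the treatment approaches used, the advice given and the number and length of treatment sessions". The practitioner part of Data analysis then says that behaviour differences between time points will be evaluated statistically from actual practice. Its sources are "patterns of referral obtained from medical record downloads for patients who consent to record reviews and from physiotherapists' case report forms". The method is fixed: "These analyses, based on patient measures, are unmatched and will follow between-group techniques i.e. unpaired t-test, chi square test and regression methods", with the regression as described for clinical outcomes. That regression is run unadjusted and "adjusted for baseline imbalances in certain variables i.e. age, gender and baseline values of key outcomes". Risk subgroup is not named.

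Entry to physiotherapy differs by phase. In phase 1 patients receive usual primary care, "with referral to other services (including physiotherapy) as usual", with no subgrouping. In phase 3 the GP tool advises against onward referral for low-risk patients, whereas "Patients at high risk of poor outcome are recommended to be referred to physiotherapy". The GP version has two categories, so its high category takes in those above the low cut-off. The recommendation is advisory: GP and patient may use it in deciding.

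**The concern.** A case report form can exist only for a patient who reaches a physiotherapist. The intervention acts on that step, because it is meant to change which patients are referred, by risk. A phase 1 versus phase 3 comparison of form data therefore conditions on something the intervention alters. If patients at different risk need different numbers of sessions, targets or treatments, those measures can move with no physiotherapist changing practice. The article itself says session numbers are flexible according to individual need.

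Objective (ii) in Study Aims concerns change in GPs' and physiotherapists' clinical behaviour, and the forms are the main record of what physiotherapists actually do. A caseload effect could be read as a behaviour effect. It could also hide one: physiotherapists who shortened care within each risk group might show no overall change if their caseload became more severe.

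**Working it through.** The article gives no figure for this comparison, so there is none to reproduce. The check asks how far mean sessions per referred patient could move with practice held fixed.

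**Input from the article.** Expected risk mix of back pain patients (Sample Size, Patients): 40% low, 40% medium, 20% high.

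**Assumptions, not in the article.** Referral probabilities by risk group in each phase; sessions of 2, 4 and 6 for low, medium and high risk, identical in both phases; a flatter alternative of 3, 4 and 5.

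**Formulas.** Share of risk group g among referred patients = (mix_g × referral_g) / sum over groups. Mean sessions = sum of (share_g × sessions_g).

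**Example, scenario (b).** Phase 1 referral is 30% in every group, so the referred mix stays 40/40/20 and the mean is 0.4×2 + 0.4×4 + 0.2×6 = 3.60. Phase 3 referral is 10/80/80%. The products are 0.04, 0.32 and 0.16, total 0.52, giving shares 0.077/0.615/0.308. The mean is 0.154 + 2.462 + 1.846 = 4.46, a shift of +0.86.

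| Scenario | Referral, phase 1 (low/med/high %) | Referral, phase 3 | Mean sessions, 2/4/6 | Shift | Shift with 3/4/5 |
|---|---|---|---|---|---|
| (a) | 30/30/30 | 0/100/100 | 3.60 to 4.67 | +1.07 | +0.53 |
| (b) | 30/30/30 | 10/80/80 | 3.60 to 4.46 | +0.86 | +0.43 |
| (c) | 20/30/40 | 10/60/70 | 4.00 to 4.48 | +0.48 | +0.24 |
| (d) | 10/30/50 | 10/50/60 | 4.46 to 4.44 | −0.02 | −0.01 |
| (e) | 20/30/40 | 20/30/40 | 4.00 to 4.00 | 0 | 0 |

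**Effect on the unadjusted t-test.** Further assumptions: within-group SD 2.5 and 100 versus 300 forms. The variance in each phase is 2.5² plus the variance between risk groups. For (b), SE = √(8.49/100 + 7.58/300) = 0.332 and z = 0.862/0.332 = 2.60, so the two-sided 5% test rejects 74% of the time with no change in practice. The same steps give 90% for (a), 30% for (c) and the nominal 5% for (d). These percentages ignore the adjusted regression, which would lower them by an amount the article's figures do not allow one to compute.

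**Check of the remedy.** Comparing within risk group gives a difference of 0 in every scenario, because practice within group was held fixed. In (a) the phase 3 low-risk cell is empty, so a difference standardised to 40/40/20 cannot be computed there. Standardisation has to be limited to groups present in both phases.

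**The case against.** A reader might infer that the form measures will shift even if nobody changes practice. The article does not establish that. The tool is advisory, adherence is unknown, and phase 1 referral by risk is not given. If GPs already referred selectively, as in (d), mean sessions hardly move. Scenario (a) is an extreme: it needs no low-risk patients at physiotherapy in phase 3, yet the article plans and trains for low-risk treatment there. It also uses a 6-item GP tool and a 9-item physiotherapy tool, which may classify the same patient differently. All of this stands, and it limits the claim to a possible or likely bias of unknown size.

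The planned regression adjusts for baseline key outcomes. The primary outcomes, disability and catastrophising, are described as key risk factors for chronicity and overlap with the tool's content, so adjustment would remove part of the shift. That stands too, but risk subgroup is not in the set, and the t-tests and chi-square tests adjust for nothing.

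Objective (ii) has other evidence. The same two vignettes are repeated, attitude and confidence scales are matched within practitioner, and GP measures cover all consenting patients. None is selected through referral. However, the vignettes record reported behaviour and are only described, and the scales do not measure what physiotherapists do.

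The analysis section's named examples are largely GP measures; the form items are listed under data collection. The Discussion concedes that changes may not be attributable to the intervention and says referral rates will be monitored. Still, the forms are named as a source for behaviour differences, and a changed mix of referred patients is not identified as a bias.

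Finally, stratifying a secondary process measure is often left to an analysis plan. Here, though, the article itself states the method and the adjustment variables.

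**Conclusion.** The concern holds in a limited form. For physiotherapy case-report-form items, the stated comparison can count a change in caseload as a change in physiotherapist behaviour. Under the assumptions shown, the spurious shift in mean sessions runs from about 0 to about 1 per patient before adjustment, and adjustment for baseline disability and catastrophising would reduce it. Size and direction depend on phase 1 referral by risk and on adherence to the tool.

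Two stronger readings are not supported. One is that any rise in sessions or psychological targets in phase 3 would be an artefact: the article does not give the inputs needed to show it, and physiotherapists' practice may change as well. The other is that the crude contrast is worthless: the article also asks about the process of care that patients receive, and for that question a caseload-driven change is part of the system's effect. The point affects a secondary objective and leaves the primary patient outcomes untouched.

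**What to change.** In Data analysis, Health care practitioners' attitudes and behaviour and care processes:

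- For case-report-form items used as evidence of physiotherapist behaviour, compare phases within, or adjusted for, the risk subgroup from the patient questionnaire's subgrouping tool. If one summary is wanted, standardise only over risk groups represented in both phases.
- Keep the crude contrast among referred patients, but label it a change in care delivered and not in physiotherapist behaviour.
- Optionally, report sessions per recruited patient, counting zero for those not referred. This measure does not condition on referral.

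No new data should be needed. The same section already plans to compare GP risk ratings with patients' questionnaire responses to the tool and expects agreement to rise after the intervention, which implies responses in both phases; this should be confirmed. The costs are a few sentences of analysis text, smaller cells and wider intervals. Some selection will remain within risk groups, because referral still depends on GP and patient choice.

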i) Monthly monitoring of referral rates to physiotherapy and patient waiting times in order to identify and react promptly with funding support to increase physiotherapy response to any increase in demand for the service.

j) Agreed onward care pathways for those patients felt by physiotherapists to require the services of secondary care specialists.

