## Discussion

Although it is generally accepted that randomised controlled trials provide the highest level of evidence in healthcare research, we opted for a pre-post design as it was more appropriate to study real-life implementation of a complex intervention, using multiple components and targeting multiple outcomes. Using a quasi-experimental design, the IMPaCT Back study will introduce, support and evaluate a new care system for assessing and managing LBP patients in primary care; subgrouping for targeted treatment. As such, the overall evaluation of this quality improvement study will take account of a wider range of factors than is usually seen within conventional randomised controlled trials. This includes health care practitioner attitudes and behaviour (both reported behaviour and actual behaviour), evaluation of clinical care processes, patients' clinical outcomes and cost-effectiveness of the new system.

The fluid nature of systems and structures within the NHS means that health care provision is constantly changing, and this introduces an added layer of complexity into our analysis of change in this study. Therefore, given the before/after design of the study, it may not be possible to definitively conclude that any changes we see in phase 3 are a direct result of the interventions from the IMPaCT Back study. We will, therefore, monitor other changes at national level (such as the production of new guidelines) and at local level, such as the commencement of new services for LBP patients within the PCT and changes in referral rates and waiting lists for clinical care.

There are limitations to the pre-post study design, including that any changes seen in phase 3 may be due to other influences or due to change in GP and physiotherapist behaviour during the study, for reasons other than the IMPaCT Back study. Potential Hawthorne effects are likely to be minimised given the long observational period (6 months in phase 1 and 12 months in phase 3).

This study directly addresses one of the key recommendations from the NICE [15] LBP guidelines: to evaluate screening protocols and test their effectiveness in targeting treatments for patients. If the data favour phase 3 of the IMPaCT Back study, this will provide valuable information about brief and feasible ways to screen patients with LBP in primary care, and improve their outcome by using information about their risk status at consultation.

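### The formal phase comparison of actual clinical behaviour rests on consenting patients and lists no GP or practice term, so a change in whose patients are sampled is not separated from a change in practice.

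*Protocol article*

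**What the plan says.** Changing GPs' and physiotherapists' clinical behaviour is specific objective (ii) under Study Aims. The abstract lists practitioner behaviour and the process of care among the key secondary objectives.

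- **Data source.** The Phase 1 section on practitioners' attitudes, behaviour and care processes takes actual behaviour from "anonymised GP medical record reviews and physiotherapy case report forms, for patients who consent to the study team accessing their medical records". The Data analysis section repeats this: the data are "obtained from medical record downloads for patients who consent to record reviews and from physiotherapists' case report forms".
- **Comparison.** The same section continues: "These analyses, based on patient measures, are unmatched and will follow between-group techniques i.e. unpaired t-test, chi square test and regression methods". It refers forward to the methods for clinical outcomes, where "Analyses will be carried out both unadjusted and adjusted for baseline imbalances in certain variables i.e. age, gender and baseline values of key outcomes". Neither GP nor practice is listed.
- **Contrast with attitudes.** In the same section, self-confidence and PABS scores are matched to the individual practitioner, before and after.
- **Second behaviour measure.** Practitioners answer the same two case vignettes in each phase. This needs no patient consent, but it captures reported behaviour, and differences over time are only described.
- **Referral monitoring.** The intervention includes "Monthly monitoring of referral rates to physiotherapy and patient waiting times", used to direct funding support. The Discussion undertakes to watch "changes in referral rates and waiting lists for clinical care" as part of local change. Neither is named as an outcome.

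**The concern.** The question is whether the same practitioners now do something different. The planned test asks whether two separate samples of consenting patients, pooled by phase, received different care. The two questions have the same answer only if the samples come from the same practitioners in similar proportions, and if consent relates to care in the same way in both phases.

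The documents give reasons why either condition could fail:

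- The invitation is posted after the consultation, so response can depend on what happened there, including whether the patient was referred. Referral is one of the outcomes.
- In phase 3 the subgrouping tool produces its referral recommendation within the consultation. In phase 1 there is no tool.
- GPs can opt patients out of the prompt.
- The intervention adds feedback on recruitment per GP and per practice, a funded link GP in each practice, and £10 per patient identified. Recruitment effort by individual GPs may therefore change along with the intervention.
- Patients invited in phase 1 are not re-invited in phase 3.

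If so, the study could report a change in referral or prescribing that is only a change in the sample, or miss a real one. The limitations in the Discussion concede other influences in general but mention neither GP mix nor differential consent.

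**Working it through.** **The plan's own figures.** No sample size or power is stated for the behaviour comparison; the stated power concerns RMDQ. The Sample Size section gives 45,000 adults and a lowest consultation rate of 6%: 45,000 × 0.06 = 2,700, which reproduces "we expect at least 2,700 LBP consulters per year". Recruitment runs 6 + 12 months, so 2,700 × 1.5 = 4,050 consulters. At about 50% consent that is 4,050 × 0.5 = 2,025, consistent with calling 1,000 recruits feasible. Split 1:2 by phase, 1,000 gives about 333 and 667. The number consenting to record review will be lower; the rate is not stated.

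All rates below are assumptions for illustration. True practice is the same in both phases throughout, and the test is the crude two-sided 5% comparison at 333 v 667.

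**Scenario 1: GP mix.** Two GP types refer at fixed rates a and b. The high referrers supply half the phase 1 sample and a share s of the phase 3 sample. Measured rate = (1 − s)a + sb.

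| a, b | s in phase 3 | Phase 1 | Phase 3 | Tests significant |
|---|---|---|---|---|
| 10%, 40% | 60% | 25% | 0.4 × 10 + 0.6 × 40 = 28% | about 17% |
| 10%, 40% | 70% | 25% | 0.3 × 10 + 0.7 × 40 = 31% | about 50% |
| 15%, 35% | 60% | 25% | 0.4 × 15 + 0.6 × 35 = 27% | about 10% |
| 15%, 35% | 70% | 25% | 0.3 × 15 + 0.7 × 35 = 29% | about 26% |

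Within each GP type the phase difference is exactly zero, so a comparison within GP removes the shift. Age, gender and baseline scores do not identify the GP and cannot be relied on to do so.

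**Scenario 2: response depends on care received.** With true referral p = 0.30, and response rates r among referred and n among non-referred patients, measured referral = pr / [pr + (1 − p)n].

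- Phase 3 response 60% v 45%, phase 1 response unrelated to referral: 0.180 / (0.180 + 0.315) = 36.4%, a shift of +6.4 points. The standard error is √[0.21 × (1/333 + 1/667)] = 3.1 points, so z is about 2.1 and about 52 to 54% of tests are significant, depending on the standard error used.
- Phase 3 response 55% v 50%: 0.165 / (0.165 + 0.350) = 32.0%, +2.0 points, about 10% significant.
- The same 60% v 45% in both phases: both measure 36.4%, and the phase difference is zero.

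The last line matters: selective response biases the contrast only if the selection itself changes between phases. A GP term does not remove this second kind of shift. Checking it needs data on coded patients who did not consent.

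**The case against.** Four arguments on the other side have force.

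**Behaviour is not judged only on consenting patients.** A reader might infer that it is. The documents do not support that: the vignettes give a second measure from the practitioners themselves, unaffected by patient mix. What remains is that they capture reported behaviour and are only described, so the formal test of actual behaviour still rests on consenters.

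**The comparison is not purely crude.** The word unmatched might suggest so, but regression is named, with adjustment for age, gender and baseline outcomes, and it will take out part of any shift in measured case mix. Unmatched is also simply correct for patients, because phase 3 recruits a new cohort. Neither point deals with GP mix or with response driven by the care received.

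**The documents do not show that a shift will occur.** Recruitment procedures are stated to be the same in both phases. The figure of over half false positives requires response to depend on referral in phase 3 and not at all in phase 1. It is an extreme case and should not be quoted as the expected error.

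**Coverage of 25% (1,000 / 4,050) overstates selection.** It is tempting to read this as a response rate. The 4,050 includes ineligible patients, GP opt-outs and people who consult in both phases, and 1,000 is a recruitment aim. The relevant figure for response is the roughly 50% consent.

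It might also be said that model terms belong in a fuller analysis plan. But this article itself states the unmatched approach and lists the adjusters, while choosing practitioner matching for attitudes.

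**Conclusion.** The point holds in limited form. The formal test of actual behaviour uses consenting patients, is unmatched by practitioner, and has no listed GP or practice term. A between-phase change in GP mix, or in how response depends on care, would therefore be indistinguishable from a change in practice. It could exaggerate or hide a real effect.

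Its size cannot be derived from the documents. Under the assumptions shown, shifts of 2 to 6 points in a referral rate of 25 to 30% give roughly 10 to 50% significant results where 5% is intended; with no shift there is no excess error. This concerns a key secondary objective and leaves the primary patient outcomes untouched. It is worth correcting because the GP-mix part can be removed at almost no cost.

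**What to change.** **Main change.** In the Data analysis section on practitioners' attitudes and behaviour, add GP (or practice) as a term in the process-of-care regressions, so that each GP or practice is compared with its own phase 1 behaviour. GP is preferable, since a practice term leaves shifts between GPs within a practice. The cost is a line of wording and a few more parameters (at most six for 7 practices), provided each record identifies its GP or practice.

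**Supporting check.** Where the practice system and governance allow, compare anonymised counts of physiotherapy referrals among all patients given the trigger Read Codes, by GP or practice and by phase. Report the share of coded patients that the consenting sample represents in each phase. This addresses consent selection, which the GP term does not. The cost is one aggregate query per practice.

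The check should not replace the main analysis. The counts cannot be adjusted for questionnaire case mix. They remain open to changes in coding between phases, since in phase 3 entering the code also opens the tool. They do not cover physiotherapists' treatment behaviour. The referral monitoring already planned is described within the intervention, with no documented phase 1 baseline or breakdown by GP, so it cannot be assumed to supply these counts.
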